### Statistical analysis

Statistical analysis will be conducted by an independent statistician using SAS V. 9.3 (SAS Institute, Cary, North Carolina, USA) and the Statistical Package for the Social Sciences software V. 26.0 for Windows (IBM SPSS Statistics, IBM Corp., Somers, New York, USA) will be used for the data analyses. For all analyses, the statistical significance level will be set at 5% (α = 0.05).

## Discussion

The current treatment protocols for ischaemic stroke are focused on acute ischaemic stroke, including thrombolytic therapy, antiplatelet aggregation, and neuroprotective therapy, which benefit only a small population of patients with stroke because of the narrow therapeutic time window.^15^ Most patients with ischaemic stroke are in the recovery period with obvious limb dysfunction and cognitive impairment; The intensity of interventions that have been studied to date might be inadequate.^16^

Acupuncture is recommended as a treatment for stroke in traditional Chinese medicine, and its safety has been confirmed by a wide variety of literature.^9^^,^^17^^,^^18^ However, evidence of its efficacy in previous studies has been inconclusive regarding the treatment of patients with ischaemic stroke in the recovery period.^19^ NGF, the first neurotrophic drug to be discovered, plays an active role in regulating neuronal development, differentiation, plasticity, cell death, and survival. However, NGF is mainly used for the treatment of peripheral neuropathy and is rarely used during the recovery period of ischaemic stroke.^20^^,^^21^ This is because the barrier between the brain and blood, BBB, is an obstacle to the transportation of large molecules into the brain, including those used for treating diseases of the central nervous system such as stroke and Alzheimer's Disease (AD).^22^ An intact BBB under physiological conditions and a repaired BBB under pathological conditions prevent the entry of peripheral inflammatory substances and regulate the exchange of toxins and nutrients between the brain and blood.^23^

Based on the above reasons, several studies have found that SMES is similar to an intervention method for opening the BBB and inducing the transportation of drugs, such as NGF, into the brain. Furthermore, the authors found that the opening effect on the BBB was most obvious under SMES intervention at the GV20 and GV26 meridian points.^9^ As a result, the authors selected the optimal stimulus parameter of specific stimulation mode SMES, which can contribute to the development of neuroprotective therapy, especially for facilitating the use of NGF.^24^

Stroke rehabilitation training and evaluation play important roles in stroke treatment. Patients are usually provided individual rehabilitation training plans according to their condition; therefore, the authors will strictly follow the uniform criteria for rehabilitation evaluation. The mRs can be considered the strongest predictor of subsequent quality of life.^25^ The FMA reflects the level of motor dysfunction and is widely used in the evaluation of motor dysfunction after stroke.^26^^,^^27^ The MBI is a common method for assessing activities of daily living, and the TUGT mainly calculates the time required to stand up for a walk to assess motor function in patients.^28^ The POMA scale is a useful tool for evaluating physical function and fall risk in stroke survivors.^29^ Compared with MMSE, The MoCA and LOTCA are more comprehensive and, be used clinically for cognitive impairment detection.^30^^,^^31^ Moreover, rs-fMRI is a powerful method of examining the networks of neurons involved in motor and cognitive processing and the effects of disease status on brain function.^32^ fNIRS works by using optical methods to measure changes in cerebral blood flow and oxygen saturation.^33^ Therefore, evaluation of the scales combined with rs-fMRI and fNIRS can further explain the relationship between the improvement of clinical efficacy and changes in brain function.

There are a few limitations to this study. First, the sample size calculation was based on the data from our pilot trial, which may affect the accuracy of the sample size calculation results. Second, the basic cure rate is calculated rather than considering the measurement of mRs as the primary outcome measure because efficacy assessment for the whole population during the study is necessary, and there should be scientific evaluation criteria; however, this may produce false results.

Under strict quality control, this study will potentially confirm the clinical efficacy of specific stimulation mode SMES combined with NGF for the recovery period of ischaemic stroke. This study also aims to explore the correlation between clinical efficacy and changes in brain function, which is of great significance in providing ample evidence to consolidate the theoretical basis for the application of this combined therapy.

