**Fig. 1 fig0001:**
[figure not shown]
Study Flow: Steps that all patients should go through from enrolment to analysis.

**Table 1 tbl0001:** Schedule of enrolment, interventions and assessments.

Stage	Baseline	Treatment phase				Follow-up phase	
Number of visits	1	2	3	4	5	6	7
Time point	Week 0	Week 1±1 day	Week 2±1 day	Week 3±1 day	Week 4±1 day	Week 8±3 days	Week 12±3 days
Eligibility screening	X						
Informed Consent Form	X						
Demographic characteristics	X						
Medical history	X						
Definitive diagnosis	X						
Inclusion criteria	X						
Exclusion criteria	X						
Evaluation of treatment expectation	X						
Therapeutic effect record form		X	X	X	X		
Scale assessment							
Modified Rankin Scale, mRS	X		X		X	X	X
Modified Barthel Index (MBI)	X		X		X		
Simplified Fugl-Meyer Assessment of motor function score (FMA)	X		X		X		
Timed up and go test	X		X		X		
Tinetti Performance Oriented Mobility Assessment (POMA)	X		X		X		
Montreal Cognitive Assessment (MoCA)	X		X		X	X	X
Informant Questionnaire on Cognitive Decline in the Elderly (IQCODE)	X						
Mini-mental State Examination, MMSE	X						
Loewenstein Occupational Therapy Cognitive Assessment (LOTCA)	X		X		X		
Acupuncture safety evaluation		X	X	X	X		
NGF treatment safety evaluation		X	X	X	X		
Adherence assessment					X		
Combination of medications	X						
Adverse Events		X					
Data Processing	X						
Research Completion	X						
Researcher Review	X						

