#### Inclusion criteria

The inclusion criteria include (1) Patients with first-ever ischaemic stroke confirmed by Computed Tomography (CT) and/or Magnetic Resonance Imaging (MRI); (2) 14-days to 6 months after the onset of stroke;(3) Patients between the ages of 30 and 80; (4) Modified Rankin Score (mRS), 3‒4; and Mini-Mental State Examination (MMSE) < 27; (5) Patients who are able to accept and comply with EA treatment and have good compliance; (6) A willingness to participate in the project.

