### Randomization and allocation concealment

Patients who qualify for inclusion will be recruited from March 2022 to December 2025. The recruited participants will be randomly divided into four groups by a randomization system (eBalance, Randomization and Trial Supply Management, Taimei Technology, Shanghai, China) and allocated to four groups, namely: acupuncture + placebo, acupuncture + NGF, SMES + placebo, and SMES + NGF groups.

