### Outcome measures and evaluation

The primary outcome measure will be the basic cure rate (patients with mRs ≤2 are judged as clinically cured; basic cure rate = number of participants in a group with mRs ≤2/total participants in group × 100%).^12^ The mRs score was 0‒6 points. The higher the score, the more serious the neurological deficit. The secondary outcome indicators are FMA, MBI, TUGT, POMA, MoCA, LOTCA.

Baseline data will be collected by an independent outcome evaluator on the first visit (week 0), including participants' demographic data, medical history, comorbidities, major medications, and clinical evaluation, including ECG, routine blood/urine/stool tests, electrolytes, liver/renal function examinations, as well as mRs, FMA, MBI, TUGT, POMA, MoCA, and LOTCA. At the end of treatment (week 4), patients will undergo the above examinations again and subsequently enter the follow-up period.

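### The primary result is a crude share reaching mRS ≤2 among patients who start one or two steps away; adjusting for baseline mRS and adding a full-scale mRS secondary outcome would recover precision and information already collected

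*Protocol article*

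**What the plan says.** All references are to the protocol article.

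- **Entry.** The inclusion criteria require "Modified Rankin Score (mRS), 3‒4" and an interval of "14-days to 6 months after the onset of stroke".
- **Primary outcome.** Under Outcome measures and evaluation: "The primary outcome measure will be the basic cure rate (patients with mRs ≤2 are judged as clinically cured". The measure is then defined as "basic cure rate = number of participants in a group with mRs ≤2/total participants in group × 100", a percentage per group that makes no reference to the starting score.
- **Secondary outcomes.** The same section lists them: "The secondary outcome indicators are FMA, MBI, TUGT, POMA, MoCA, LOTCA". No outcome using the whole mRS appears.
- **Collection.** The schedule in Table 1 has a row for "Modified Rankin Scale, mRS" marked at baseline and at weeks 2, 4, 8 and 12. The Follow-ups section confirms mRS at the two follow-up contacts.
- **Stated limitation.** In the Discussion, "the basic cure rate is calculated rather than considering the measurement of mRs as the primary outcome measure". The reason given is that efficacy must be assessed for the whole study population. The authors add that this choice could give a false result.
- **Sample size.** The calculation uses two crude proportions, 75% and 50%, and arrives at 55 per group before allowance for dropout.
- **Statistical analysis and randomisation.** The Statistical analysis section names software and a 5% level, but no test, model or covariate. The randomisation section says "The recruited participants will be randomly divided into four groups by a randomization system" and gives no detail on stratification.

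**The concern.** The threshold is not equally far away for everyone. A move from 3 to 2 is a cure and a move from 4 to 3 is nothing, though each is one step on the same scale. Worsening from either starting score is counted the same as no change. The stated reason for the dichotomy, assessing efficacy in the whole population, points towards the full scale, which uses every patient's outcome.

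If the starting score predicts reaching mRS ≤2, as the unequal distance suggests, a crude comparison leaves that predictor unused. The cost is a wider confidence interval and lower power than the same patients could give. A treatment effect among patients who start at 4 may also go largely unseen, because the authors name the weakness of the dichotomy but list no outcome that answers it.

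**Working it through.** **1. The plan's own figure.** Inputs from Sample size calculation: p_T = 0.75, p_C = 0.50, α = 0.05 (two-sided reproduces the stated figure), power 0.80.

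n = (1.960 + 0.842)² × [0.50×0.50 + 0.75×0.25] / 0.25² = 54.94, so 55 per group. The figure reproduces, and it is a crude two-proportion calculation.

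**2. Evaluable number used below.** 288 in total is 72 per group; 72 × 0.8 = 57.6, taken as 58. This is also the size at which the usual pooled two-proportion test reaches 80% (unrounded n = 57.67).

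**3. Assumptions.** The article gives neither the baseline 3/4 mix nor cure rates by baseline score. Assumed: half the patients at mRS 3; control cure rates (baseline 3 / baseline 4) of 50/50, 60/40, 65/35 or 70/30, each averaging 50%; and a treatment effect that is a common shift on the logit scale and gives 75% overall in the SMES + NGF arm.

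**4. Power.** Simulated trials, 58 per arm, two-sided 5%. The crude two-proportion test is compared with a Cochran–Mantel–Haenszel test stratified by baseline mRS.

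| Control cure, baseline 3/4 | Crude | Stratified by baseline mRS |
|---|---|---|
| 50/50 (not prognostic) | 80% | 80% |
| 60/40 | 80% | 82% |
| 65/35 | 80% | 83% |
| 70/30 | 80% | 86% |

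The last three rows come from 4,000 runs each. A repeat with 20,000 runs gave 81.7%, 83.1% and 85.3% for the stratified test, so the last entry is better read as 85 to 86%. Varying the share at mRS 3 from 30% to 70%, and the baseline odds ratio for cure from 1 to 10, put the stratified test at 80% to 90% and the crude test at 79% to 82%. Type I error was 4% to 6% for each test.

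**5. Chance imbalance.** Total 95% sampling range of the crude difference: 1.96 × √[(0.25 + 0.1875)/58] = ±0.170, about ±17 points.

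The part due to unequal shares at mRS 3 is 1.96 × √[(g₀² + g₁²) × 0.25/58]. Here g₀ and g₁ are the gaps in cure rate between baseline 3 and baseline 4 in the control and treated arms. The common logit shift narrows the gap in the treated arm.

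| Control rates | g₀ | Treated rates | g₁ | 95% contribution | Share of variance |
|---|---|---|---|---|---|
| 60/40 | 0.20 | 0.824/0.676 | 0.148 | ±3.2 points | 4% |
| 65/35 | 0.30 | 0.860/0.640 | 0.220 | ±4.8 points | 8% |
| 70/30 | 0.40 | 0.8935/0.6065 | 0.287 | ±6.3 points | 14% |

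For 70/30: √[(0.160 + 0.0824) × 0.25/58] = 0.0323, and 1.96 × 0.0323 = 0.063. The share of variance is (contribution / 17.0)². These amounts lie inside the ±17 points and are not added to it.

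**6. Full scale.** A baseline-stratified rank test on the whole mRS, simulated under proportional odds over the wider range in step 4, had 90% to 99% power. That figure depends on the proportional-odds assumption and on an assumed spread of scores, so it shows direction only.

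**The case against.** The strongest reply is that nothing here is an error. Randomisation makes the crude comparison valid. Chance imbalance in baseline mRS is ordinary sampling variation, already covered by the standard error and the 5% level. Cure against shift is a defensible choice of endpoint, and the authors explain theirs and list it as a limitation. The power gain is a few points on assumed inputs, and nil if baseline mRS is not prognostic. All of this stands.

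Three stronger readings are tempting, and the article does not support them:

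- **That the primary analysis will be unadjusted.** A sample size formula and the definition of a rate do not fix the test. The Statistical analysis section neither includes nor excludes covariates, and a full protocol or analysis plan may settle this.
- **That randomisation ignores baseline mRS.** The article gives no stratification detail either way.
- **That imbalance distorts the result by an extra amount, or that the full mRS will never be analysed.** The first misreads sampling error as bias. For the second, the article shows only that no such outcome is on its list.

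What the reply does not remove is what the article states outright: the entry range, the threshold, the crude definition, and a secondary list with no full-scale mRS outcome beside a conceded weakness of the dichotomy.

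**Conclusion.** The point holds as a worthwhile improvement to the stated plan, not as a flaw that invalidates it. The loss is in precision and in information: improvement from 4 to 3 and any worsening do not count. Under the assumptions in the working, adjustment adds about 2, 3 or 5 to 6 points of power to a crude 80%. It removes a source of variation worth about ±3, ±5 or ±6 points within a total of ±17. The size rests on the unknown baseline mix and on how strongly baseline mRS predicts cure. With no prognostic value there is no gain and essentially no loss. No claim is made that covariates or stratification are absent from the trial.

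**What to change.** Before unblinding, and if the full protocol or analysis plan does not already do so:

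- Prespecify the primary comparison adjusted for baseline mRS (3 versus 4), for example by logistic regression. Report it as a standardised risk difference with a 95% confidence interval, and show the raw cure rates beside it.
- Add the ordinal mRS shift as a secondary outcome: proportional odds, adjusted for baseline mRS, at the same time point as the primary outcome, with a stated place in the testing order.

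This needs no more patients, visits or data, since baseline mRS is recorded at week 0 and mRS is already scored at every later time point concerned. It is not wholly free. The adjusted estimate has to be explained to readers who expect two percentages, and the shift analysis assumes a roughly common effect across mRS levels. No change to the randomisation is proposed: the article does not describe its stratification, and it gives recruitment as starting in March 2022.

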## Conclusion

This protocol describes a multicentre, randomized, placebo-controlled trial that aims to assess the efficacy and safety of specific stimulation mode SMES combined with NGF in reducing the recovery period of ischaemic stroke and provide evidence-based medical data. The results of this research will help provide the latest and high-quality evidence for clinicians and policymakers seeking innovative and effective ways to treat patients with ischaemic stroke.

## Trial registration

ClinicalTrials.gov Identifier NCT05231694.

## Trial status

Patient recruitment will begin in March 2022 and is expected to finish at the end of 2025.

## Patient consent

Obtained.

## Ethics approval

The ethics committees of the Third Affiliated Hospital of Zhejiang Chinese Medical University, Ningbo Hwamei Hospital, and Lishui Second People's Hospital approved the study.

## Data sharing statement

The data used to support the findings of this study have been deposited in the Clinical Trials repository whose ID is NCT05231694. The URL is https://clinicaltrials.gov/ct2/show/NCT05231694.
